**Arm A: control group**					
	From the 1st to the 3rd day	1 tablet every 2 hours	6 tablets	—^a^	
	From the 4th to the 12th day	1 tablet every 2.5 hours	5 tablets	No smoking from the 5th day	
	From the 13th to the 16th day	1 tablet every 3 hours	4 tablets	No smoking	
	From the 17th to the 20th day	1 tablet every 5 hours	3 tablets	No smoking	
	From the 21st to the 25th day	2 tablets a day	Up to 2 tablets a day	No smoking	
**Arm B: maintained therapy 1**					
	From the 1st to the 3rd day	1 tablet every 2 hours	6 tablets	—	
	From the 4th to the 12th day	1 tablet every 2.5 hours	5 tablets	No smoking from the 5th day	
	From the 13th to the 16th day	1 tablet every 3 hours	4 tablets	No smoking	
	From the 17th to the 20th day	1 tablet every 5 hours	3 tablets	No smoking	
	From the 21st to the 25th day	2 tablets a day	Up to 2 tablets a day	No smoking	
	From the 26th to the 50th day	2 tablets a day	Up to 2 tablets a day	No smoking	
**Arm C: maintained therapy 2**					
	From the 1st to the 3rd day	1 tablet every 2 hours	6 tablets	—	
	From the 4th to the 12th day	1 tablet every 2.5 hours	5 tablets	No smoking from the 5th day	
	From the 13th to the 16th day	1 tablet every 3 hours	4 tablets	No smoking	
	From the 17th to the 20th day	1 tablet every 5 hours	3 tablets	No smoking	
	From the 21st to the 25th day	2 tablets a day	Up to 2 tablets a day	No smoking	
	From the 26th to the 50th day	2 tablets a day	Up to 2 tablets a day	No smoking	

^a^Not applicable.

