**Methods:**

A prospective, multicenter, open-label, controlled, parallel, phase IV clinical trial of 402 smoker patients prepared to quit smoking. The study was conducted in 10 hospitals in Spain. A control group is compared to 2 intervention groups in which the duration of the drug is increased without increasing its dose, administering half and all, respectively, of an additional marketed container that includes 100 tablets. Thus, participants will be randomized to three groups in a 1:1:1 ratio to receive cytisinicline: (1) a control group treated with cytisinicline according to the usual clinical guidelines and product information (25 days); (2) a group with a 50-day cytisinicline regimen (an additional 25 days at a dose of 1.5 mg every 12 hours), seeking to increase its efficacy while minimally impacting adherence; and (3) a group with a 75-day regimen (an additional 50 days at a dose of 1.5 mg every 12 hours), attempting to increase its efficacy, although the longer duration of the drug may threaten adherence. Efficacy in the 3 arms will be analyzed through sustained abstinence at 6 and 12 months, point abstinence rate assessed every 7 days, and abstinence rate from Day 25 to Day 50 and from Day 25 to Day 75 in the 3 study arms. (1) The variation in withdrawal and craving symptoms in the 3 groups, (2) safety through the percentage of adverse events in the 3 treatment arms, and (3) economic impact by evaluating the cost-effectiveness and cost-utility ratios of the 2 prolonged regimens versus the usual clinical cytisinicline regimen. To calculate the differences between the 3 groups for each outcome variable, a univariate analysis will be performed. Statistically significant variables will be included in a multivariate model.

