## Methods

### Trial Design

Phase IV randomized, open-label, controlled, parallel, multicenter clinical trial in patients who are candidates for smoking cessation to demonstrate the superiority of maintenance therapy with cytisinicline compared to the standard regimen.

The trial was designed according to the standardized guide for interventional trial protocols, SPIRIT (Standard Protocol Items: Recommendations for Interventional Trials statement [Multimedia Appendix 2]). A total of 402 patients from 10 smoking cessation units in Spain will be randomized. Recruitment will last for one year, with a follow-up of 52 weeks per patient recruited. Candidate patients who sign the informed consent form will be randomized to 3 possible arms in a ratio of 1:1:1.

Arm A: control group. Participants randomized to this group will be treated with cytisinicline as stated in the data sheet. They must remain smoke-free from day 5 of treatment.

Arm B: maintained therapy 1. Following the standard regimen, these patients will maintain treatment for an additional 25 days at a dose of 1.5 mg twice daily.

Arm C: maintained therapy 2. Following the standard regimen, these patients will maintain treatment for an additional 50 days at a dose of 1.5 mg twice daily (see Table 1).

At the end of the treatments, participants will continue in the follow-up phase, without treatment, until completing 52 weeks in the study (see Figure 1).

**Table 1 table1:** Dosage guidelines in each of the 3 treatment arms.

Days of treatment		Recommended dosage	Maximum daily dose	Recommendations	

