### Intervention

Cytisinicline is administered as 1.5 mg tablets to all patients for 25, 50, or 75 days depending on arm allocation. The drug is produced and marketed by Adamed Pharma SA [name] (Poland).

According to the data sheet for cytisinicline, the D-day will be set as the date from which the smoker intends to quit smoking. This date cannot be later than the fifth day after the start of treatment with cytisinicline. This D-day should be decided by the patient with his doctor before starting treatment.

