### Specific Outcomes Efficacy

Different outcomes will be used to measure the efficacy of cytisine in each arm of the clinical trial.

The sustained abstinence rate will be determined in each of the three treatment arms at 6 and 12 months, based on carbon monoxide co-oximetry results in ppm. The correlation between the sustained abstinence rate in each of the three arms studied at 6 and 12 months, based on co-oximetry results, and the self-reported abstinence at 6 and 12 months will be calculated.

Additionally, point abstinence will be analyzed every 7 days in each of the 3 arms studied, based on the results obtained in the CO tests.

The percentage increase in abstinence rates will be compared with the increase in the duration of cytisinicline use. The number needed to quit smoking for one patient in each treatment group will also be calculated.

Interval abstinence will also be determined in this clinical trial. The abstinence rate will be analyzed from Day 25 to Day 50 in all 3 study groups and from Day 25 to Day 75 in all 3 study arms. The abstinence rate will also be determined from Day 25 (usual arm), Day 50 (extended arm 1), and Day 75 (extended arm 2) up to 6 and 12 months.

Relapse rates will be analyzed in each treatment arm. The frequency and percentage of relapses will be determined in those who quit smoking from Day 25 (usual arm), Day 50 (extended arm 1), and Day 75 (extended arm 2) up to 6 and 12 months in all 3 arms.

Craving and withdrawal symptoms will be assessed during the clinical trial. The mean Minnesota Nicotine Withdrawal Scale (MNWS) score and the mean craving score will be calculated at the initial in-person visit in all 3 arms, and their change from this visit will be measured on days 25, 50, and 75 in all 3 study arms.

Predictors of continued abstinence at 6 and 12 months of treatment and of relapse (clinical, anthropometric, demographic, and smoking-related variables) will be determined in all study arms.

Quality of life in each group will be calculated using the EQ-5D-5L scale score at baseline, 50 days, 90 days, 6 months, and 1 year.

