## Results

Trial recruitment and patient registration will conclude in November 2026. Follow-up for all participants will continue until December 2027. At the time of this writing, we have 12 preselected patients at the sponsoring center (Smoking Unit, University Hospital Complex of Santiago de Compostela, Spain) who meet the exclusion and inclusion criteria of the study and who will begin the initial visit in the coming days.

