This is a low-intervention study due to several characteristics: (1) studies of extended regimens exist in the European Union [23]. These analyze the efficacy and safety of extended cytisinicline treatments of 40 and 84 days. We also have experience with extended doses of 1.5 mg every 12 hours for 3 months [24]; (2) modifications to drug administration are minimal. One of the study arms corresponds to the regimen used in daily clinical practice; and (3) patient selection was performed according to the drug’s prescribing information. All of this ensures its feasibility.

Unlike other studies that propose a substantial change in the dose and frequency of the molecule, this one uses extended treatment regimens of an additional 25 and 50 days, with minimal modification to the commercially available drug formulation. Thus, in Spain, each pack of cytisinicline contains 100 tablets, so one-third of patients will be randomized to take half the tablets contained in the additional pack (2 tablets a day for an additional 25 days) and another third to take all of them in that pack (2 tablets a day for an additional 50 days). Furthermore, these regimens, with their lower administration frequency, could be more adherent than regimens of 3 times a day for 12 weeks.

At the time of this writing in Europe, the same dose and duration of cytisine are used for all smokers. However, smokers represent a heterogeneous patient population with differences in dependence, emotionality, motivation, and comorbidities. This study, using a multivariate model, allows the identification of the group of patients who would require extended treatment with cytisinicline, personalizing its use in routine practice.

It is a multicenter study conducted in different geographical areas of Spain, with a representative sample. Moreover, it is carried out by a research group with experience in the diagnosis and treatment of smoking cessation. Patients treated in 10 specialized smoking cessation units accredited by scientific societies are included. Furthermore, this is an independent trial, free from the financial interests of the pharmaceutical industry, which enhances the rigor of the results. Funding for disseminating the results will be obtained through grants or public funds.

This trial incorporates the calculation of the economic impact of extended doses, determining the savings for the National Health System that these regimens could generate by increasing the number of ex-smokers.

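### Table 1 gives Arm C the same dosing schedule as Arm B, ending at day 50; the text gives Arm C 75 days, so the last row should run to day 75

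*Protocol article*

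**What the plan says.** Table 1 (Dosage guidelines in each of the 3 treatment arms) has one block per arm. Arm A has five rows, the last being "From the 21st to the 25th day". Arm B repeats those five rows and adds a sixth for its extension, days 26 to 50 at 2 tablets a day. Arm C has the same six rows, and its last is also "From the 26th to the 50th day" at 2 tablets a day. The table footnote follows directly.

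The text describes Arm C differently, and does so consistently:

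- Abstract, Methods: "a group with a 75-day regimen (an additional 50 days at a dose of 1.5 mg every 12 hours").
- Trial Design: after the standard regimen, "these patients will maintain treatment for an additional 50 days at a dose of 1.5 mg twice daily (see Table 1").
- Intervention: tablets are given "for 25, 50, or 75 days depending on arm allocation".
- Specific Outcomes Efficacy: abstinence after treatment is counted from Day 25 in the usual arm, "Day 50 (extended arm 1), and Day 75 (extended arm 2").
- Discussion, Principal Findings: one third of patients take half of the additional 100-tablet pack, and "another third to take all of them in that pack (2 tablets a day for an additional 50 days").

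**The concern.** The trial compares three durations of one drug, so the day on which treatment stops is the experimental variable. Table 1 is the only table in the article that gives dosing by day range, and the Trial Design sentence that defines Arm C refers the reader to it. As printed, the table shows no difference between Arms B and C.

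If a site dispensed from the table, or from material copied from it, an Arm C patient would stop at day 50. That patient would have received Arm B treatment while being analysed as Arm C, with post-treatment abstinence counted from Day 75. Any such cases would pull the Arm C result towards that of Arm B and weaken the evidence on the longest regimen. The article reports that "we have 12 preselected patients at the sponsoring center", about to have their initial visit at the time of writing, so the correction is best made early.

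**Working it through.** **Inputs.** Row lengths and maximum daily doses come from Table 1. The extension lengths come from Trial Design: 25 further days for Arm B and 50 for Arm C, at 1.5 mg twice daily, that is 2 tablets a day. The pack size of 100 tablets comes from the Discussion.

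**Step 1: duration according to the text.** Total days = standard days + extension.
- Arm B: 25 + 25 = 50 days.
- Arm C: 25 + 50 = 75 days.

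This reproduces the 25, 50 and 75 days stated in the Intervention section.

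**Step 2: maximum tablets in the standard phase (Table 1, identical in all arms).**

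| Days | Number of days | Maximum per day | Tablets |
|---|---|---|---|
| 1–3 | 3 | 6 | 18 |
| 4–12 | 9 | 5 | 45 |
| 13–16 | 4 | 4 | 16 |
| 17–20 | 4 | 3 | 12 |
| 21–25 | 5 | 2 | 10 |
| Total | 25 | | 101 |

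**Step 3: add the extension.**

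| Schedule | Extension days | Extension tablets | Last day | Maximum tablets |
|---|---|---|---|---|
| Arm B, text and table | 25 | 25 × 2 = 50 | 50 | 101 + 50 = 151 |
| Arm C, Table 1 as printed | 25 | 25 × 2 = 50 | 50 | 101 + 50 = 151 |
| Arm C, text | 50 | 50 × 2 = 100 | 75 | 101 + 100 = 201 |

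**Step 4: the gap for Arm C.**
- Days: 75 − 50 = 25.
- Tablets: 201 − 151 = 50.
- Dose: 50 × 1.5 mg = 75 mg.

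**Step 5: check against the pack.** The Discussion says that Arm C uses the whole additional pack: 50 days × 2 tablets = 100 tablets, exactly one pack. The printed Arm C block uses 50 tablets, half a pack, which is what the Discussion assigns to Arm B. The pack arithmetic therefore supports the text and not the table.

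**Step 6: the corrected row.** With the last Arm C row running from day 26 to day 75, the extension is 75 − 25 = 50 days and 100 tablets, ending on day 75. This agrees with every statement in the text.

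**The case against.** Nobody reading the article as a whole would be misled. The sentence that points to Table 1 itself states the 50-day extension, the Abstract, Intervention and Discussion agree, the efficacy outcomes anchor Arm C at Day 75, and the visit calendar includes a day-75 contact. On this view one table row is mistyped or missing, no analysis depends on it, and the shortfall of 50 tablets would arise only if a site followed the table against the text. The article condenses a fuller protocol, and nothing shows that sites dispense from it. A row could also have been lost when the PDF was converted to text: the layout of Table 3 is visibly disturbed, and the trial design figure, which might give the durations, is not available here. Finally, the window before the preselected patients start may already have closed.

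Much of this stands. The intended regimen is clear, and the effect on site materials is unknown. The shortfall measures the discrepancy at maximum daily doses and is not a forecast of under-treatment. A lost row cannot be fully excluded, but it is unlikely: the Arm C block has all its cells and runs straight into the footnote, whereas the faults in Table 3 are misalignments and not demonstrated row losses. Had the original been a single row to day 75, the conversion would have had to alter the day number itself.

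None of this makes the table right. It is the article's day-by-day schedule for the variable under test, and it is wrong for one arm of three.

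**Conclusion.** The point holds. In the text as supplied, the Arm C block of Table 1 contradicts the rest of the article, and the table is the part in error. Taken literally it is 25 days and 50 tablets (75 mg) short, 151 tablets against 201 at the maximum daily doses, and makes Arm C identical to Arm B.

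This should be corrected, but it does not threaten the design: the text settles the intended regimen, and sample size, power and significance level do not depend on the row. The conclusion assumes that the extracted table matches the printed one. That a copied Arm B block is the cause is the likeliest explanation, not an established fact.

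**What to change.** In the Arm C block of Table 1, change the last row to cover days 26 to 75 at 2 tablets a day. Alternatively, keep that row and add one for days 51 to 75 at 2 tablets a day; both give the same regimen.

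Then check the dispensing instructions, patient sheets and case report form for the same error, ideally before the preselected patients start. If patients are already on treatment, make the check before any Arm C patient reaches day 50, or as soon as possible if some have passed it.

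The cost is one table row and a check of site materials. Design, sample size and analysis stay as they are.

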**Figure 1 figure1:**
[figure not shown]
Trial design. Recruitment will last for one year, with a follow-up of 52 weeks per patient recruited.

### Study Population

This study will be conducted in the Smoking Cessation Units (SCU) of 10 Spanish hospitals with different levels of complexity of care that provide care to active smokers who wish to quit smoking. An SCU is defined as a health care service integrated within a health area that promotes, coordinates, and implements actions to prevent and treat smoking in that area, in direct collaboration with the area’s health care services. The main objectives of SCUs are clinical care, education, research, and management [26]. The SCUs are accredited by the Spanish Society of Pneumology and Thoracic Surgery and by a public agency. Their geographical distribution is representative of the Spanish population (see Table 2).

**Table 2 table2:** Smoking Cessation Units (SCU) of 10 Spanish hospitals, with different levels of complexity of care, that provide care to active smokers who wish to quit smoking.

Recruitment centers	Estimated number of patients
University Clinical Hospital of Santiago de Compostela	42
Galdakao Hospital, Bilbao	30
San Pedro de Alcántara Hospital, Cáceres	60
San Carlos Clinical Hospital, Madrid	90
October 12 University Hospital, Madrid	40
Clinic Hospital, Barcelona	30
Alcorcón Foundation Hospital, Madrid	30
Virgen de la Macarena University Hospital, Sevilla	40
University Clinical Hospital of Valencia	20
Virgen de la Victoria Hospital, Málaga	20

The sample size of the Cytisinicline Treatment for Smoking Cessation–Long-term Study (CITISILONG) trial (N=402) is based on a minimum number of patients for each of the treatment arms. The sample size calculation is given in the Statistical Analysis section of the Methods section.

### Recruitment

A recruitment period of 3 weeks is envisaged, where the persons in charge of the SCU participating in the study will identify patients who come to the practice with the intention to quit smoking and verify and select individuals who meet the abovementioned selection criteria. Written informed consent will be obtained at the screening visit. Once the consent is signed, the patient will have the first trial visit within a maximum of 15 days. Recruitment will be noncompetitive, and each site is allocated a predetermined number of patients (see Figure 1).

### Eligibility Criteria

Male and female smokers over the age of 18 years who have smoked more than 10 cigarettes per day during the past year and during the month before the screening visit are eligible to participate in the study. Smokers must also be prepared and motivated to quit smoking (score of 7 or higher on the visual analog scale of motivation). Smokers who have received pharmacological treatment for nicotine dependence (nicotine replacement therapy, varenicline, bupropion, or cytisinicline) within the previous 3 months are excluded from participating in the clinical trial.

In addition, exclusion criteria (Textbox 1) have been designed, taking into account the considerations of the drug label. All patients meeting all inclusion criteria and no exclusion criteria are consecutively invited to participate until the calculated sample size is obtained in each center.

Exclusion criteria for the study.Renal and/or hepatic insufficiency.Over 65 years of age (due to limited clinical experience).Hypersensitivity to the active substance or to any of the excipients.Unstable angina.Recent personal history of acute myocardial infarction or recent stroke (less than 8 weeks).Clinically relevant arrhythmias or uncontrolled hypertension.History of psychiatric illness with and without treatment (panic disorder, psychosis, bipolar disorder, and depression) within the last 12 months.History of alcohol or other drug abuse within the last 12 months.Use of tobacco products other than cigarettes, e-cigarettes, or marijuana in the past month and did not agree to abstain from using these products during study participation.Patients being treated with antituberculosis drugs.Patients being treated with drugs metabolized by CYP1A1 (cytochrome *P* 450 family 1, subfamily A, polypeptide 1) and CYP1A2 (cytochrome *P* 450 family 1, subfamily A, polypeptide 2), especially those with a narrow therapeutic margin (eg, theophylline, tacrine, clozapine, and ropinirole).Pregnant or breastfeeding smokers.Women on systemic hormonal contraceptives.

### Patient Enrollment and Randomization

All participants who consent to participate and who meet the eligibility criteria will be included in the trial and randomized. They are recorded in the data collection booklet designed specifically for this purpose.

Randomization will be performed in 2 phases. First, using a simple randomization procedure, participants are assigned to 1 of the 3 arms in a ratio of 1:1:1 (This is already mentioned in Study design).

Then, as noncompetitive recruitment is proposed, the sites are randomized (1 to 8, unrestricted) so that randomization determines where to start distributing the randomized sequence in the first phase. A randomization list will be generated using SAS 9 software (SAS Institute Inc) for Windows. This process will be carried out at the coordinating center, and each participating center will be provided with its own list according to the number of patients allocated. The aim is to achieve a balanced randomization in the treatment groups in the overall sample. There are no blinding techniques, as this is an open-label study. Blind-breaking procedures are therefore not applicable.

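### Pre-generated allocation lists go to the centres of an open-label trial with no concealment described, and the site-ordering step counts 8 sites where the trial has 10

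*Protocol article*

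**What the plan says.** All of the following is in the Protocol article.

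- **Method** (Patient Enrollment and Randomization): "using a simple randomization procedure, participants are assigned to 1 of the 3 arms in a ratio of 1:1:1". No blocks or strata are mentioned.
- **Site step** (same section): "the sites are randomized (1 to 8, unrestricted". Its purpose is to decide where distribution of the sequence begins.
- **List handling** (same section): the list is generated in SAS, and "This process will be carried out at the coordinating center". Then "each participating center will be provided with its own list according to the number of patients allocated".
- **Blinding** (same section): "There are no blinding techniques, as this is an open-label study".
- **Stated aim** (same section): "The aim is to achieve a balanced randomization in the treatment groups in the overall sample".
- **Who recruits** (Recruitment): the persons in charge of each smoking cessation unit identify, verify and select patients, within a fixed quota per site.
- **Invitation** (Eligibility Criteria): eligible patients are invited consecutively.
- **Number of sites** (Study Population): "Smoking Cessation Units (SCU) of 10 Spanish hospitals". The Abstract agrees: "The study was conducted in 10 hospitals in Spain". Trial Design and the Discussion also give 10, and Table 2 lists ten quotas.

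**The concern.** In an open-label trial, allocation concealment is the main protection against selection bias at entry. The section describes how allocation is handled: a complete list is made in advance and a site-specific portion goes to each centre. It mentions no sealed envelopes, no central web or telephone release, and no separation between the list holder and the recruiter.

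Three other parts of the article raise the stakes:

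- Entry depends partly on judgement, since a motivation score of 7 or more is required.
- The Discussion and Conclusions already expect longer treatment to do better, so a preferred arm exists.
- Under Trial Monitoring, each site's own investigators or a delegate do the monitoring, so no independent check on use of the list is described.

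If patients with a better prognosis were steered to one arm, the planned regression could adjust only for what was measured and retained by its P<.20 and Akaike selection.

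Separately, an allocation procedure that counts 8 sites in a 10-site trial contains a wrong or unexplained figure.

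**Working it through.** **1. Concealment: the passages side by side.** The list exists before recruitment and is given to the centre (Patient Enrollment and Randomization). Staff at the centre choose the patients (Recruitment). Past and current treatment are visible to all (open-label). Nothing in the article stands between the list and the recruiter.

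**2. Size of the possible bias (assumed inputs; the article gives none).** Let *f* be the fraction of places in each of two arms that are steered, and *g* the gap in quit probability between favourable and unfavourable smokers. If one arm gains the favourable smokers and the other the unfavourable ones, the spurious difference is 2 × *f* × *g*.

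The last column shows what this does to one pairwise test. It assumes both arms truly quit at 30% (the article's control rate) with 134 per arm (402 / 3). The standard error is √(2 × 0.30 × 0.70 / 134) = 0.056. The rejection rate is P(Z > 1.96 − bias/SE) + P(Z < −1.96 − bias/SE).

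| *f* | *g* | Bias = 2*fg* | Two-sided type I error (nominal 5%) |
|---|---|---|---|
| 2% | 10 points | 0.4 points | 5.1% |
| 5% | 20 points | 2 points | 6.5% |
| 10% | 30 points | 6 points | 18.8% |

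Sample Size Determination plans 30% against 50% for the longest regimen, a 20-point difference. For the middle regimen it gives 45% in words and .40 in brackets, so the difference from control is 15 or 10 points. The top scenario is 6/20 = 30% of the largest planned difference; the bottom one is negligible.

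**3. Site count.** The Table 2 quotas are 42 + 30 + 60 + 90 + 40 + 30 + 30 + 40 + 20 + 20 = 402, over ten sites. The eight smallest sum to 402 − (90 + 60) = 252 and the eight largest to 402 − (20 + 20) = 362. No eight sites account for the full sample, so 1 to 8 cannot be a complete ordering of this trial's sites.

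**4. Balance under simple randomisation.** The standard deviation of an arm's size is √(N × 1/3 × 2/3) = √(402 × 2/9) = 9.5, around 134. In 400,000 simulated sequences the median gap between largest and smallest arm was 18, and exact balance occurred in 0.2%. The effect on power is small: for 30% against 45%, 134/134 gives 72.0% and 120/148 gives 71.3%, a loss of 0.7 points.

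**5. Predictability if blocks were introduced.** With a fixed, known block size at an open-label site, guessing the arm with most places left in the block is right 61% of the time (size 3), 56% (size 6) or 53% (size 9). A concealed simple list gives 33%.

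**The case against.** The strongest reply is that the article never says the list is open. It does not say who at the centre holds it, whether it is sealed, or whether lines are revealed one at a time. Open-label describes treatment, not the list. The article condenses a fuller protocol, which may name a safeguard. This stands: a reader might infer that recruiters do see the next arm, but the text supports only that the list is at the centre and no concealment is described. The point remains because the article states the mechanism, and that mechanism, followed as written, does not protect allocation.

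Other parts of the reply also hold:

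- **Consecutive invitation**, and randomising only consenting, eligible patients, limit selective recruitment. They do not hide the next assignment.
- **The interval between consent and first visit**, up to 15 days, might suggest that order could be manipulated. The article does not say when in that interval allocation happens, so nothing is built on it here.
- **The 8-site step** might be read as leaving two sites without any part of the sequence. The same section gives every participating centre a list matching its quota, so no such gap is shown. What is shown is a figure that conflicts with the rest of the article.
- **Simple randomisation** is valid. The stated aim is balance overall, not by site, and the power cost is under 1 point.
- **Counselling** might be taken to differ between centres. Limitations says only that it may, and adds that a standardised model is in place.

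**Conclusion.** The concern holds in two parts. First, as written, each centre of an open-label trial receives a pre-generated list, centre staff select the patients, and no concealment is described. The resulting bias cannot be estimated from the article. Under the assumptions shown it ranges from about 0.4 to about 6 points with no drug effect, and the 6-point figure is the top of that range, not an expected value. This part deserves correction before recruitment because selection at entry cannot be reliably removed afterwards. It rests on the article alone; a safeguard in the full protocol would answer it.

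Second, the 1-to-8 site step contradicts the 10 sites given in the Abstract, Trial Design, Study Population with Table 2, and the Discussion. This is certain from the text, though its practical consequence is not established.

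That simple randomisation does not secure the overall balance aimed for is a minor, optional matter.

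**What to change.** **Needed**

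- Keep the list at the coordinating centre. Release each assignment singly, and only after consent, confirmed eligibility and baseline data are recorded. If the full protocol already provides this, say so in the article.
- Correct the site step to 10 sites, or delete it.

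**Optional**

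- If overall balance is wanted, use varying block sizes that are not disclosed to the sites, with central release retained, and adjust the analysis for site. Block sizes should not be published or fixed: staff in an open-label trial know past allocations, so central release alone does not remove the predictability shown above.

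**Cost.** N stays at 402 and no visits are added. Enrolment is slightly slower, because each centre must obtain an assignment from the coordinating centre. The allocation procedure must be revised in a trial that is already authorised. Results reports 12 preselected patients about to begin, so the change should be made before they are allocated.
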